## Abstract

**Background:**

Despite its proven efficacy in reducing recurrence and improving survival, adherence to endocrine therapy (ET) is suboptimal in women with breast cancer (BC). Health-related quality of life (HRQoL) in BC has been widely studied and many positive effects have been highlighted. Recently, a link between HRQoL and compliance with ET has been suggested, which would suggest a potential role for HRQoL assessment in improving compliance with ET. With the advent of digital technologies, electronic collection of HRQoL on a tablet is now possible. Thus, we hypothesize that systematic HRQoL assessment (using a tablet, prior to each consultation, with presentation of scores to clinicians) coupled with therapeutic information could have an impact on 12-month compliance with ET in patients with non-metastatic BC.

**Methods:**

In this study, we will include 342 women with non-metastatic hormone receptor–positive BC with an indication for treatment with ET. Patients will be randomly assigned 1:1 by minimization and stratified by age, stage, type of ET prescribed, and presence of comorbidities (or not) in two arms. The intervention will consist of numerical HRQoL assessment using the CHES (Computer-based Health Evaluation System) software before each consultation (with delivery of scores to clinicians) coupled with therapeutic information. Therapeutic information will consist of three workshops related to understanding the prescription, nutrition, and fatigue. A reminder letter will be sent to patients every month. Patients in the control group will follow standard care. HRQoL will be assessed using a classic “paper-pencil” collection at baseline in both arms to ensure comparability between arms and at 12 months. The primary endpoint is 12-month compliance with ET. Patient satisfaction with care and the clinicians’ perception of the usefulness of routine HRQoL assessment will also be assessed.

**Discussion:**

This study will allow clinicians to identify and better understand the areas in which patients who receive ET have difficulties and thus it will assist clinicians with patient management. Systematic evaluation of HRQoL could provide an additional endpoint for measuring patients’ health status and treatment-related symptoms, including ET. If the results of this study are positive, this intervention could be proposed as an integral part of daily clinical practice in patients who receive ET.

**Trial registration:**

ClinicalTrials.govNCT04176809. Registered Nov. 25, 2019.

## 1. Background

Currently, a large number of hormonal and cytotoxic oral therapies are available for breast cancer (BC) management. The major advantage of these therapies is their convenience due to self-administration [1, 2]. Currently, in cancer treatment, more than 40 oral drug specialties are reimbursed by the French health insurance system [1]. These oral forms present a new challenge in oncology, namely concerning treatment compliance. Compliance is defined as the extent to which the patient follows the prescriber’s recommendations [3]. Oral anticancer therapies raise concerns about poor compliance, particularly the impact of adverse effects due to non-compliance on clinical outcomes. Non-compliance compromises overall efficacy of oral therapies and potentially leads to treatment failure [4].

In BC, the oral form of endocrine therapy (ET) is by far the most widely investigated in terms of compliance [1]. Compliance with oral ET is not optimal in BC. Indeed, only 59% of women who receive ET for BC remain compliant one year after prescription [5] and this percentage ranges between 41% and 72% at the end of 5 years of treatment [6]. Poor compliance with ET is associated with decreased survival [7, 8], increased risk of recurrence [7], and poor prognosis [9]. To improve compliance, several studies [10–12] have implemented interventions via educational materials (letters, information booklets, and telephone interviews) but none has shown a significant effect. Hadji et al., in their study testing the addition of educational materials to standard therapy versus the standard therapy only in women taking anastrozole, have shown no significant effects on compliance and persistence with adjuvant anastrozole [10]. In a study by Ziller et al., patients receiving additional/supplemental information appeared to have an improved adherence rate, even though differences between groups with regard to the primary endpoint were not statistically significant [11]. In another study, postmenopausal women with hormone receptor–positive (HR^+^) early-stage BC treated with aromatase inhibitors (AIs) were randomly assigned to one of two groups: one receiving only AIs and the other one receiving educational materials plus AIs. This study has shown that education materials do not improve compliance in this patient population and has highlighted the complex nature of compliance and persistence [12].

It is interesting to note that compliance is a multidimensional phenomenon that can result from various factors related to patients (social support, patient beliefs, and psychosocial factors), treatments (side effects), or health-care systems (poor patient–health-care provider relationship) [13].

Evaluation of the quality of care is of major importance, but to date, most quality initiatives have focused on assessing adverse events, clinical processes, and cost variables. Less attention has been given to indicators of clinical improvement measured from the point of view of the patient [14]. To give patients the opportunity to express their perception concerning their own health in clinical trials and routine practice, it is necessary to plan and assess the use of health-related quality of life (HRQoL) in clinical research and practice (Fig. 1).

**Fig. 1 Fig1:**
[figure not shown]
Schedule of enrolment, interventions, and assessments

HRQoL is gathering increasing interest in oncology, as reflected by the number of scales being developed and the increased use of HRQoL measurement as an outcome in randomized controlled trials. Reasons for this growing interest may be related to significant treatment toxicities but also to the fact that HRQoL has been shown to be a prognostic factor for survival [15, 16]. In many cases, symptom palliation of and improvement of HRQoL, rather than increased survival, are the main goals of treatment. Thus, the American Society of Clinical Oncology and the US Food and Drug Administration recommend HRQoL as the second endpoint after overall survival and the primary endpoint of treatment efficacy if treatment has no effect on overall survival. Over the past decade, HRQoL in BC has been widely studied and many determinants have been identified [17, 18].

Routine evaluation of HRQoL was shown to have a positive impact on communication between patients and medical staff [19] and on clinical parameters such as the duration of treatment without relapse and survival [20, 21]. Recently, it has been suggested that there may be a link between HRQoL and compliance with oral ET. Indeed, Pinheiro et al. reported that women with poorer HRQoL were more likely at risk of non-adherence [22] in a study addressing the association between HRQoL and under-use of ET in women with hormone-sensitive BC. This result suggests that focusing on a modifiable factor such as HRQoL could be a way to improve compliance with oral ET. In addition, to date, the modulatory effect of HRQoL on compliance with oral treatments in BC has not been studied.

With the advent of digital technologies, it is now possible to perform HRQoL measurements using a tablet with instantaneous score generation [23]. This mode of measurement provides real-time results to clinicians (through graphics) and generates alerts (color codes) if HRQoL scores are deteriorated, allowing adjustment of patient support in a personalized way. From the patient’s point of view, the inclusion of numerical assessment in the process of data collection has shown benefits in disease management and symptom control [24], improving survival [20] and patient-clinician communication [19]. Moreover, it potentially facilitates clinical decision making through the systematic and continuous collection of symptom data [25].

Since compliance is a multidimensional phenomenon, any attempt to improve it should encompass several potential contributors. Thus, we hypothesize that electronic measurement of HRQoL (before each consultation with scores communicated immediately to clinicians who can discuss it with patients), coupled with therapeutic information, will improve 12-month compliance rate with ET in patients with non-metastatic BC. At a later step, we will assess the role of social support and psychological distress as potential modulators of compliance with ET, the capacity of HRQoL to predict compliance with ET, patient satisfaction with care, and physician perception regarding the clinical utility of routine HRQoL evaluation.

## 2. Methods

To achieve study aims, we will carry out a randomized, interventional, prospective study. Patients will be recruited at the Dijon cancer center (Georges François Leclerc-Unicancer Centre) in France. This center is specialized in cancer management; therefore, clinicians are experienced in patient HRQoL evaluation and are accustomed to take this criterion into consideration in routine patient management.

Women who are at least 18 years old and have non-metastatic HR^+^ BC will be included in this study. These women will have to be at the end of primary treatment, have an indication for ET treatment during 5 to 10 years, be affiliated with a French social security scheme or the beneficiary of such a scheme, and have agreed to participate by providing written consent. Patients who participate in another clinical trial where HRQoL is assessed will not be included, nor will women for whom HRQoL evaluation is not possible (cognitive disorders, psychiatric disorders, and people who do not speak French).

### 2.1. Inclusion procedure

The study will be proposed to eligible patients by their doctors (oncologists, surgeons, and radiation oncologists). Patients will be included at the time of the first prescription of ET (at the end of the treatments by surgery with or without chemotherapy with or without radiotherapy). Once included, patients will be randomly assigned to one of the two study arms (interventional arm or control arm). Patients then will be referred to the clinical research associates, whose role will be to collect patient data (clinical and sociodemographic) in both study arms and to instruct patients in the interventional arm on how to use the CHES (Computer-based Health Evaluation System) software [26]. For patients who wish to access the platform from home, a username and password will be provided. If needed, clinical research associates will assist patients to complete HRQoL questionnaires. This information will be collected in the case report form to take into account social desirability bias.

### 2.2. Randomization

Eligible patients who agree to participate will be randomly assigned to one of two parallel arms (ratio 1:1) by the minimization technique with stratification by age, stage, presence or absence of comorbidities, and type of ET prescribed.

### 2.3. Intervention arm

#### 2.3.1. Assessment of HRQoL

The intervention will consist of an electronic measurement of patient HRQoL before each consultation with delivery scores to clinicians, who can discuss it with patients and couple it with therapeutic information. Before their consultation, patients will complete the EORTC-QLQ-C30 and the EORTC-QLQ-BR23 questionnaires via a touch pad or from their home via a secure web portal. Patients will complete the questionnaires via the CHES software [26]. The CHES software was developed by ESD (Innsbruck, Austria) in collaboration with the EORTC Quality of Life Group to facilitate the inclusion of HRQoL measurement instruments in research projects and daily clinical practice. This mode of collection provides clinicians with real-time results and generates alerts in the event of clinically significant deterioration of patients’ HRQoL scores, allowing them to tailor treatment. The scores then will be generated and provided to patients and clinicians in a graphic form, describing scores course. Access to the CHES web portal will be open to patients outside consultation time points to enable them to monitor HRQoL if necessary. In case of HRQoL minimal impairment (a decrease lower than 20 points) [27], self help tools can be generated, providing patients with indications on how to deal with certain adverse effetcs. In the other hand, in case of significant impairment of HRQoL (a decrease higher than 20 points) [27], the clinical research assistant will receive an alert and if, necessary, she will the information to the medical team for appropriate care.

#### 2.3.2. Therapeutic information

Therapeutic information will consist of workshops on various themes and will be coordinated by a pharmacist in charge of therapeutic education at the Dijon cancer center. This health-care professional will be responsible for the organization and implementation of these workshops. Workshops will be performed by pharmacists, nurses, or dieticians. Only at workshop 1 will attendance be required; other workshops will be optional.

Workshop 1 will deal with “understanding the prescription”. The aim is to inform patients of their ET and treatment benefits. It also helps patients to recognize and react to the occurrence of possible adverse effects and anticipate their occurrence through appropriate preventive means. This workshop will be held within 2 months after the first prescription of ET and will be performed by pharmacists with training in therapeutic education.

Two additional optional workshops on nutrition (workshop 2) and fatigue (workshop 3) will be offered. These workshops will be collective and performed by dieticians and nurses, respectively. Workshop 2, on nutrition, will focus on the benefits of exercise and the need to adopt an appropriate diet. Patients will have the opportunity to express their representations and experiences related to their diet and the consequences of disease and treatments on diet. Workshop 3, on fatigue, will address the recognition of fatigue and early management of this symptom. Patients can describe their experiences of fatigue and how their life is affected by it. Moreover, they can identify possible causes and finally discuss solutions to better this symptom.

Every month, a letter encouraging patients to regularly take their medication will be sent. This letter, derived from the work of Hadji et al. [10], will include some tips on how to deal with some particular side effects of ET.

#### 2.3.3. Control arm

Patients in the control arm will receive standard care. They will not undergo digital HRQoL collection, and therapeutic information workshops will not be proposed. This information will be taken into account when performing statistical analyses.

For both arms, HRQoL will be evaluated at baseline using the FACT-G (Functional Assessment of Cancer Therapy - General) questionnaire to ensure the comparability of groups concerning HRQoL at inclusion and again at 12 months. This HRQoL assessment will be performed using a traditional paper questionnaire, and scores will not be provided to clinicians. Anxiety and depression, social support, and patient satisfaction with care will also be assessed in both arms at baseline and 12 months after.

### 2.4. Endpoints

#### 2.4.1. Primary endpoint

The primary endpoint of this study is 12-month compliance with ET as evaluated using the Morisky Green Levine (MGL) scale. Patients will be considered to be compliant if they have a high adherence in the MGL scale.

#### 2.4.2. Secondary endpoints

The secondary endpoints will be anxiety and depression assessed by the Hospital Anxiety and Depression Scale (HADS) questionnaire, social support assessed by Sarason’s Social Support Questionnaire (SSQ6) questionnaire, and HRQoL assessed by the FACT-G questionnaire. HRQoL data using the FACT-G questionnaire will be assessed at inclusion in both arms to ensure comparability between groups and at 12 months to assess the predictive value of HRQoL on compliance with ET. Patient satisfaction with care will be assessed by the EORTC-SAT-C33 and EORTC-OUT-PATSAT-7 questionnaires. Physician perception regarding the utility of systematic HRQoL evaluation will be assessed using an ad-hoc questionnaire derived from the work of Velikova [19, 28], including the perceived utility and satisfaction of routine assessment HRQoL, reasons for use/non-use, and the intention to adopt this assessment in routine care.

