#### 2.6.2. HRQoL analysis

All HRQoL scores will be calculated according to FACT-G guidelines and described according to the arm (interventional arm or control arm). A logistic regression model will be used to assess the capacity of HRQoL to predict 12-month compliance with ET. The modulatory potential of social support on compliance will be assessed using an interaction term between the availability/satisfaction of social support that patients receive and HRQoL in a logistic regression model. The modulatory potential of psychological distress on compliance will be assessed using an interaction term between patient anxiety/depression and HRQoL in a logistic regression model.

An analysis of missing HRQoL data profiles will also be performed. If a missing not at random (MNAR) profile is demonstrated/suspected, multiple imputation of missing data can be performed in sensitivity analysis, taking into account the variables associated with the occurrence of missing data.

The significance level for the statistical analyses is fixed at a *P* value of less than 0.05, and all tests will be bilateral. The data analysis will be performed by using Statistical Analysis System (SAS) version 9.4 (SAS Institute Inc., Cary, NC, USA).

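### The 12-month FACT-G is assigned to predict 12-month compliance, so this secondary analysis gives a concurrent association and cannot show prediction

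*Protocol article*

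**What the plan says.** Section 2.4.2 gives the two FACT-G assessments separate purposes. The first "will be assessed at inclusion in both arms to ensure comparability between groups". The second is made "at 12 months to assess the predictive value of HRQoL on compliance with ET".

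The outcome is fixed in Section 2.4.1: "The primary endpoint of this study is 12-month compliance with ET as evaluated using the Morisky Green Levine (MGL) scale".

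Section 2.3.3 confirms that both arms complete the FACT-G on paper only twice, "to ensure the comparability of groups concerning HRQoL at inclusion and again at 12 months". The other scales follow the same timetable: "Anxiety and depression, social support, and patient satisfaction with care will also be assessed in both arms at baseline and 12 months after".

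The analysis is in Section 2.6.2: "A logistic regression model will be used to assess the capacity of HRQoL to predict 12-month compliance with ET". The effect of psychological distress is examined "using an interaction term between patient anxiety/depression and HRQoL in a logistic regression model", and social support is handled in the same way. None of these sentences says whether the baseline or the 12-month score enters the model.

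The end of Section 1 (Background) lists the capacity of HRQoL to predict compliance among the aims to be addressed at a later step.

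**The concern.** Prediction requires that the predictor be known before the outcome. Read as written, Section 2.4.2 pairs a score taken at 12 months with compliance assessed at 12 months, so the direction of any association cannot be established.

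The article itself supplies a reverse route. Section 1 lists side effects of treatment among the factors behind poor compliance, and the monthly letter in Section 2.3.2 deals with side effects of ET. A woman who skips or stops ET may feel better at 12 months because she is not taking it. That would work against the association that motivates the trial, where Section 1 cites a study in which "women with poorer HRQoL were more likely at risk of non-adherence". The 12-month score also comes after randomisation, and the intervention is meant to act on HRQoL, so the score may partly carry the effect of the assigned arm.

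At stake is one secondary aim: whether HRQoL marks out in advance the women who will not comply.

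**Working it through.** **Comparing the sections.**

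1. Outcome: MGL compliance at 12 months (Section 2.4.1).
2. Purpose given for the baseline FACT-G: comparability of the arms (Sections 2.3.3 and 2.4.2).
3. Purpose given for the 12-month FACT-G: predictive value for compliance (Section 2.4.2).
4. FACT-G time points available in both arms: baseline and 12 months only (Section 2.3.3). The electronic EORTC assessments before consultations belong to the intervention arm, and Section 2.6.2 scores HRQoL by the FACT-G guidelines. No intermediate FACT-G could therefore serve as predictor.
5. Nothing in the article names the baseline FACT-G as predictor or places the 12-month FACT-G before the MGL.

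The only FACT-G score assigned to prediction is thus contemporaneous with the outcome.

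**The plan's own figure.** Section 2.4.3 does not bear on the timing problem, but it supplies the size of the illustration. With 59% against 74%, two-sided alpha 5% and power 80%, the mean proportion is 0.665 and

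n = [1.960·√(2·0.665·0.335) + 0.842·√(0.59·0.41 + 0.74·0.26)]² / 0.15² = (1.308 + 0.555)² / 0.0225 ≈ 154.3, rounded up to 155 per arm, as stated.

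This gives 2 × 155 = 310 evaluable patients, with about 66.5% compliant over both arms.

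**Illustration. The association, correlation and ET effect below are assumptions; the documents give none of them.**

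- Baseline score q0: standard normal.
- Compliance C: logit P(C = 1) = ln(0.665/0.335) + ln(OR)·q0, with a true OR per SD of 1.0, 1.3 or 1.5.
- 12-month score: q12 = 0.6·q0 + 0.8·e − d·C, with e standard normal. Here d is the amount, in SD, by which taking ET lowers HRQoL in compliant women.
- Logistic regression of C on q0, and separately on standardised q12; 600 simulated trials for each setting.

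Mean odds ratio for the 12-month score. In brackets is the share of trials with an odds ratio below 1 at p < 0.05.

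| d (SD) | true OR 1.0 | true OR 1.3 | true OR 1.5 |
|---|---|---|---|
| 0 | 1.00 (2%) | 1.17 (0%) | 1.27 (0%) |
| 0.2 | 0.81 (42%) | 0.96 (4%) | 1.04 (1%) |
| 0.3 | 0.73 (72%) | 0.87 (19%) | 0.93 (9%) |
| 0.5 | 0.60 (99%) | 0.70 (82%) | 0.76 (59%) |
| 0.8 | 0.42 (100%) | 0.50 (100%) | 0.55 (100%) |

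The baseline score recovers its assumed odds ratio in every row. That is true by construction and is not evidence for the baseline analysis.

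**Check by hand.** Compliant and non-compliant women differ by about ln(OR) SD at baseline. Of this, 0.6·ln(OR) carries over to 12 months and d is taken off, so the 12-month log odds ratio is roughly 0.6·ln(OR) − d.

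- At d = 0: exp(0.6·ln 1.3) = 1.17 and exp(0.6·ln 1.5) = 1.28, which is the attenuation seen in the first row.
- Sign change at d = 0.6·ln(OR): 0.6 × 0.262 = 0.16 SD for OR 1.3, and 0.6 × 0.405 = 0.24 SD for OR 1.5.

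On the grid simulated, the mean is first below 1 at 0.2 SD and 0.3 SD respectively. A stronger correlation between the two scores would raise the crossing point, and a weaker one would lower it.

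**The case against.** The strongest reply is that Section 2.4.2 states why data are collected and does not specify a model. Section 2.6.2 says only HRQoL, and neither section bars the baseline score. The analysis is secondary and deferred, both scores will be in hand, and an association at 12 months is valid under its proper name. The baseline FACT-G, taken at the first ET prescription (Section 2.1), also cannot show deterioration on treatment, which is what the intervention monitors.

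Part of this stands. It lowers the severity, and it is a reason to keep the 12-month analysis as description. It does not remove the point. Section 2.4.2 affirmatively gives prediction to the 12-month score, so an analysis plan that used baseline would depart from it. If baseline was meant, the sentence still needs correcting.

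A reader might infer four stronger things, and the documents support none of them:

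- *The estimate will have the wrong sign.* This depends wholly on d. At d = 0 there is attenuation only. Non-compliant means any MGL score below 4, so it includes the moderate group (2 or 3, Section 2.5.2), and an average difference of several tenths of an SD over that whole group is unproven. The one direction the article cites is that poorer HRQoL goes with non-adherence.
- *The models wrongly leave out study arm.* Section 2.6.2 lists no covariates at all, which a condensed article may leave to the analysis plan. Section 2.3.3 also says that the control arm's lack of digital collection and workshops will be allowed for in the analyses.
- *The HADS and SSQ6 interaction models are wrong.* Their time point is not stated. They share the problem only if 12-month scores are used.
- *The clinical use proposed in the article would be misled.* The Discussion (Section 3) proposes adopting the intervention if the study is positive. It does not propose selecting women by this regression.

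**Conclusion.** The point holds at moderate severity and concerns a secondary objective. As written, predictor and outcome coincide at 12 months, so the aim of predicting compliance cannot be answered, whatever the effect of ET on HRQoL turns out to be. That conclusion rests on the text alone.

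The size of the distortion cannot be derived from the documents. Under the assumed model, the association is attenuated if taking ET does not change HRQoL, and reversed on average from about 0.2 to 0.3 SD upwards for true odds ratios of 1.3 to 1.5 per SD. Reversal is a possibility to guard against, not a forecast. The randomised comparison of compliance between arms is unaffected.

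**What to change.** In Sections 2.4.2 and 2.6.2:

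- Name the baseline FACT-G as the predictor of 12-month compliance, with arm in the model.
- For consistency, state that the interaction models use baseline HADS and SSQ6 with the baseline FACT-G.
- Report the 12-month FACT-G by arm as an outcome.
- Call any analysis of 12-month FACT-G against 12-month compliance a concurrent association, and do not describe it as prediction.

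The cost is wording in the protocol and the analysis plan. Section 2.3.3 shows that all the baseline questionnaires are already completed in both arms, so no visit, form or patient is added. The one loss is that the baseline score says nothing about deterioration on treatment. Keeping the 12-month association as a descriptive analysis covers that.
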